### **Project Description:**

## **The ConVenTu-study (Control of Ventilation Tubes)**

**- A randomized, controlled multicenter study -**

### **Background**

Ventilation tubes (drains) in the ear drum are one of the most common operations on children both in Norway and internationally (1,2). This intervention is performed to better hearing and speech development and to reduce ear complaints (3). Long term results of drain treatment are under discussion (4,5). A Cochrane report from 2010 concluded that drains had a positive effect on hearing in children with secretory otitis, but that effect was reduced after six to nine months (6). A systematic review of children with recurrent otitis concluded that drain insertion reduced the incidence of acute otitis with only one episode in the first six months after operation (7). Despite this, when this operation is performed follow up is planned to make sure that the drains are functioning, hearing is bettered, and potential complications are properly diagnosed and treated (8). Examples of complications are running ears, blocked tubes, early or lack of drain extrusion, persistent perforation of the ear drum or cholesteatoma (9).

According to national guidelines children are to be controlled until the middle ear is air filled and normalized, or the best possible result is attained, which can take several years. The first control is recommended after one month and thereafter every 4th month (10) while other countries have made follow up less comprehensive (11). A Scottish study found that few controls resulted in interventions and recommended that children be controlled after 3 months and thereafter only as needed (12). Swedens SBU (Statens beredning for medicinsk utvärdering) wrote in 2008 that there is no documented assessments of how and when a child who has had implanted drains should be followed up (13).

In Norway children are primarily followed up in hospital or by Ear-Nose-Throat (ENT) doctors in private practice who have operated on them, with time intervals which vary from hospital to hospital. This often occurs less often than that which is recommended by guidelines. Many hospitals have problems completing these controls within the planned timeframe, due to long wait-lists and lack of capacity. Even though most hospitals still control all children who undergo drain operations themselves, St. Olavs Hospital implemented a change in 2007. From then controls of those children assumed to be the most healthy who received drains were delegated to their GP, while children with serious

hearing loss or other medical syndromes were controlled at hospital. GP controls were 6 and 18 months after the operation and guardians would have to order the control appointments for themselves. This follow up was evaluated through a retrospective study that did not find any difference in hearing, middle ear fluid or ear complaints 2 years after the operation (14). Another study on the same material showed that children came to GP controls even though they were not called in, but many children were controlled by both GP and ENT regardless of where controls were originally planned (15).

There were, however, many limitations in this study. These included the small amount of material, the lack of randomization and that complications were not controlled over and above re-operations. In addition to this many GPs were unsure of how they should perform these controls (unpublished, own data). We would therefore like to perform a new and larger study to give more strength to recommendations nationally and internationally on the follow up of children after the implantation of drains. We will randomize children into two groups: ENT follow up and GP follow up as needed.

A potential benefit of follow up after intervention in hospital, may be the specialized equipment required for follow-up, while a potential benefit of GP controls may be short travel time and easier accessibility. As of now we know little about parents/guardians expectations to the intervention and follow-up as well as how this is experienced. We would therefore like to perform a qualitative part to this study.

### **Goals**

The overall goal of the study was to find out if controls after drain implantation in the ear drum can be performed as needed by the GP without it having negative consequences for the patient. We also wish to examine if differing follow up after the drain implantation in the ear drum effects the long term effects of the operation.

The primary endpoints are the childrens' hearing two and four years after the operation and secondary endpoints are fluid in the middle ear, number of re-operations, subjective complaints, complication rate and patient satisfaction. Our nullhypothesis is that there is no difference in hearing and other effect variables, and the alternative hypothesis is that there is a difference.

The qualitative part of this study has, as a goal, to collect new information from parents/guardians to children between the ages of 3-10 years who receive implanted middle ear ventilation tubes. The goal is to gather knowledge about guardians expectations with drain treatment and follow-up. Semi-structured interviews of guardians from both follow-up groups will provide new and important information from users of health care services and contribute to overall knowledge base.

We wish to also undergo a health-economic analysis to calculate the course of the patients' treatment/follow up for patients in both the specialist and primary health care systems using data from the Norwegian patient register (NPR) and Control and payment of health refunds (KUHR) now Municipal patient and user register (KPR). This will provide insight into costs for differing levels of healthcare and knowledge about quality of life adjusted life years as a consequence of this intervention.

The results of this study are expected to be published in at least 3 articles which will form part of a PhD degree.

### **Consequences**

The results of this study will contribute to giving increased knowledge on the follow/up of children after drain insertion in the ear drum. If the study should show that GP controls are defensible it will challenge today's situation of hospital based controls. That GPs perform controls will in this case give economic benefits. Alternatively, there may be consequences for the hospitals who already delegate controls to GPs if the study shows that children do not receive the follow up they require.

### **Materials and Methods**

The parents of children are invited to participate in the study upon their outpatient appointment for assessment to drain insertion. They receive written information including the point of the study. The study additionally requires an audiological consultation with either an audiographer or doctor at the hospital before the operation as well as one at 2 and 4 years postoperatively. In addition to this they will be required to fill out questionnaires at all three timepoints. Self-reporting forms will contain amongst other things the validated OM 8-30 questionnaire which aims to broadly describe children's ear complaints and situation over the last 3 months (16). In addition to this quality of life will be recorded using The Pediatric Quality of Life (PedsQL) where we will use the parent reported forms for children dependent on how old they are (forms can be found for 2-4 year olds, 5-7 year olds and 8-12 year olds)(17, 18) and the Strengths and Difficulties Questionnaire's Norwegian version (SDQ-Nor)(19). Previous audiological information will be collected from the journal system for example preoperative hearing and dates for previous drain insertions.

In the qualitative part of this study an individual semi-structured interview will be conducted of a choice of guardians from both follow-up groups from up-to 3 timepoints; within the first 14 days, 6 and 24 months after drain insertion.

Data from NPR and KUHR/KPR will be collected for the health economic analyses (see examinations and measurements page 7)

## **Design and procedure**

Randomized multicenter study where the primary goal is childrens change in hearing. Other audiological data, number of reoperations, subjective problems, complication rate and patient satisfaction will also be examined. We will follow the CONSORT rules. Questions regarding enrollment in the study as well as consent occur at the outpatient clinic prior to operation for children who are planned in to operation. Inclusion and randomization occur immediately after the child's operation. This, to prevent the inclusion of patients who would later be stricken from the operating list. Data collected from those who are not operated on will be shredded.

Children will be randomized to follow up after operation to either the hospital or to the GP. Follow-up through the hospital involves a control every 6 months as long as there is a clinical need for it. GP controls will only be performed as required. Guardians will be given written information as to when drain controls are recommended through their GPs; for example with ear secretion, persistent reduced hearing, ear infection, etc. GPs will receive a procedure for controls and how one should tackle the most common complications. This procedure will be attached to the discharge report from drain insertion so that it will be available for the GP under the consultation.

## **Randomization**

Stratified sampling with "center" as stratum (balances within each center) and block randomization will be used to assure like distribution at almost all timepoints. One applies for help of the department for applied clinical research, DMF, NTNU, for help with the practical part surrounding completion of randomization as well as the computer program ("WebCRF") which is used for registration and randomization.

## **Inclusion Criteria**

Children 3-10 years of age who receive an implanted drain through St. Olavs Hospital, Molde Hospital, Ålesund Hospital, Kristiansund Hospital, Gjøvik Hospital Innlandet and Stavanger Universityhospital. The lower age bracket is set to allow for hearing tests of children. The upper age bracket is set as children older than 10 years of age at initial operation often have additional illnesses which would prevent them from being candidates in this study.

## **Exclusion Criteria**

Medical syndroms or other serious comorbidities which give an expected higher complication rate after drain insertion, such as Downs syndrome, cystic fibrosis or primary ciliary dysfunction. Diagnosed auditory processing disorder (APD). Known, serious

sensorineural hearing loss in at least one ear ( $> 50\text{dB}$  hearing threshold in one frequency between 0,25 and 4,0 kHz).

Parents of children who do not master Norwegian both written and spoken.

### **Number of participants**

The calculation of the number of participants was performed by the statistician. The number depends on which factors which are to be analyzed and which statistical method will be used. We are interested in determining differences in effect of treatment in disfavor of the GP-group, but a better result in this group would be optimal in regards to the clinical implications (performing therefore a two sided test. No difference between groups is also a possibility and of interest (equivalence study). With a focus on the likeness between groups it is especially important to avoid falsely concluding “no effect” (type II error), which implies that we want a high power for the test for difference between groups, minimum 90%, preferably up to 95%.

The primary end-point is hearing, which is measured in dB (continuous variable). We examine changes in average hearing in the frequencies 0,25-4,0 kHz between 2 timepoints. The smallest clinically relevant change in hearing is 5dB. With an expected bettering of 10dB in the one group and 5dB in the other group (absolute diff. 5dB), and estimated standard deviation of 10dB in each group, we would with a significance of 5% need 85 (105) participants in each group to determine a difference with 90% (95%) power. To account for skew from the normal distribution, at least 15% should be added (increase to 98 or 131 in each group) and an additional 20% for drop-outs. A minimum of at least 118(157) participants in each group would be required. To maintain power in a model where we account for study center (random factor), and other clinical or demographic factors, the number must be increased (by at least 10 cases per variable. The total is now increased from 314 to 400, 200 participants in each group due to multiple participating hospitals.

Analysis of categorical variables require generally speaking a larger data material to reach a similar strength to continuous, normally distributed variables. The incidence of fluid in the middle ear (categorical variable) is expected to come in 80-90% of patients prior to operation. Given an expected amelioration of 90% in the one group and 85% in the other group (absolute difference in proportions of 0.05), we need to include at least 920 (1110) patients in each group to reach a strength of 90% (95%) for this statistic test. With a strength of 80%, which is acceptable to find a difference between groups (and less focus on mistakenly keeping the null hypothesis), the number would be reduced to 680. This number will be hard to achieve within the boundaries set for this project. A larger

statistically significant difference between groups would still be possible to find (generalizable to the population).

Around 800 children per year are operated on at the six participating hospitals together. We assume that around 600 of these are actual for our study, the rest will most likely be excluded due to comorbidity or age. Some will reject inclusion in the study. In a timeframe of 1-2.5 years for the inclusion of patients, and in economical bounds, it is realistic to include a maximum of 400 participants in this study, 200 randomized to each group. For categorical variables this is acceptable despite not having increased participants per study center because we assume that there are little demographic differences between study centers.

In the qualitative part of the study a choice of guardians of included children in the ConVenTu-study will be invited. The guardians will be recruited from multiple, but not necessarily all, participating hospitals (St Olavs Hospital and hospitals in Kristiansund, Molde, Ålesund, Innlandet Gjøvik and Stavanger). We will include guardians to children from both follow up groups, and with differing ages, sexes and socioeconomic backgrounds. The inclusion will occur until desaturation is achieved. We expect the amount to not exceed 20 guardians from each follow up group. Participants are informed both orally and written and a separate consent will be signed should they want to participate. Participants will not be required to bind themselves to all three interviews at the first interview.

### **Preoperative examinations and measurements**

1. Self report form where audiograph and other health care personell at the audiological center/outpatient clinic enter the guardians' answers into a database («Web-CRF»). Information about ear complaints, subjective hearing and sociodemographic background questions, operation form and questionnaires regarding quality of life "OM 8-30", "PedsQL" and "SDQ".
2. Hearing testing, including puretone audiometry (0.25-4.0 kHz) (20) and speech audiometry (21). Should the child due to age or othe reasons be unable to cooperate with these tests, other test methods may be used, for example TEOAE (transient otoacoustic emissions)(22). Speech audiometry is performed using child lists, one syllable words, two syllable words or three word utterances or speed test three word utterances (23).
3. Tympanometry (pressure measurement)(24).

### **Examinations and measurements 2 and 4 years after operation**

1. Self report form where audiograph and other health care personell at the audiological center/outpatient clinic enter the guardians' answers into a database («Web-CRF»). Information about ear complaints, subjective hearing and sociodemographic background questions, operation form and questionnaires regarding quality of life "OM 8-30", "PedsQL" and "SDQ".
2. Audiological testing as before operation.
3. Journal examination in regards to complications and new drain operations.
4. If required the GPs journal may be requested.

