### **Health Economic Examinations after 2 and 4 year follow ups**

1. Data from NPR and KUHR/KPR:

Date of treatment, diagnosis and procedure codes (ICD-10 and NCSP)

Type and length of treatment (day, full day or outpatient)

Costs (DRG-code, DRG-weight and corrected DRG-weight)

Level of care (hospital, GP, GP acute and emergent)

Reimbursement code and information regarding patient payment (HELFO)

In the qualitative part of this study an individual semi-structured interview will be conducted of a choice of guardians from both follow-up groups from up-to 3 timepoints; within the first 14 days, 6 and 24 months after drain insertion. The interview guide will at each timepoint have neutral and open questions about themes that contain the guardians' expectations and experiences related to the operation or follow up after drain operation. Themes which spontaneously come up under the interview will be explored further.

All interviews are planned to be completed by the same researcher with a length not normally exceeding 60 minutes. Interviews will be performed with the help of recording and transcribed verbatim. Interviews will be performed such that personal information is protected. The original interviews are planned to be completed in person at the institution near the patient for example their associated hospital or by home visit. The Covid-19 pandemic required the use of telephones for these interviews.

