### **Statistical analysis**

Linear mixed model (LMM) with center as random factor will be used to examine if there is a significant long-term effect (at 2 and 4 years) of treatment (insertion of drain) on hearing level and other audiological and clinical factors. Interaction joints will be included in the statistical model to examine the effect of treatment, measured in the form of change compared to pre-operative measurements, is the difference between patients who receive

follow-up through their GP or hospital. Log transformation of data will be actual if it is relevant to study relative over absolute changes, and transformation of data will be actual if a response variable appears to be skewed. Alternative non-parametric models can be used as needed.

Differences between the two randomization groups (hospital, GP) taking into account severity of complications, number of reoperations and proportion of re-referrals under the follow up period will be examined with the help of chi-squared tests (as a categorical variable) or Mann-Whitney test of differences of the entirety. It will also be actual to compare groups taking into account re-operation rate, and identify riskfactors for recurrence (re-operation), by using different types of survival analysis models, alternatively a logistic regression (if one can not account for time for re-operation).

If there is no significant difference between groups, we will focus on magnitude of differences between groups. With a lack of significant difference we will use a 95% confidence interval for absolute difference around 0 (around 1 for relative difference), but border values in the interval must be less than that which is considered a clinical difference of significance. What these values are will depend on which factors are being analyzed.

The health economic analyses will be performed based on randomization and where follow up has been performed.

In the qualitative portion of the study the transcription of interviews will be done continuously. Multiple researchers belonging to the research group and the project will collaborate to read and analyze the transcript. The analysis method will be adjusted to the data and presented problems.

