## 4. Introduction

### 4.1 Background and rationale

Otitis media with effusion is a major cause of acquired hearing problems in children. Operative treatment with the implantation of ventilation tubes (VTs), also called tympanostomy tubes or grommets, is indicated in cases of persisting or recurrent otitis media. This is the most common ambulatory surgery performed on children, and in Norway approximately 6700 children undergo surgery annually. Post-operative controls are predominantly carried out by otolaryngologists within the specialist health care system and may continue for two or more years. These controls are performed to assess whether the tubes are functional, whether hearing loss has improved and to properly treat potential complications. A meta-analysis performed in 2001 concluded that sequelae after VTs are most often transient or cosmetic in nature. VT removal is recommended after 2 years if they have not been spontaneously expelled. This is done to reduce the risk for a persistent perforation of the tympanic membrane.

The ConVenTu study is a multicenter randomized non-inferiority study which compares the hearing of patients treated with tympanostomy tubes where controls were performed by a general practitioner (GP), to those controlled within the specialist health care system. The aim is to determine whether controls performed by the GP are a safe and sufficient alternative to those controlled within the specialist health care system.

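### Complication rate is compared between arms from a journal review in which the GP's journal is optional, so complications treated wholly by the GP risk being missed more often in the GP arm

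*Combined protocol and SAP*

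**What the plan says.** The protocol, under Goals, lists complications among the secondary outcomes: "secondary endpoints are fluid in the middle ear, number of re-operations, subjective complaints, complication rate and patient satisfaction". Its Statistical analysis section compares the two randomised groups "taking into account severity of complications, number of reoperations and proportion of re-referrals under the follow up period", using chi-squared or Mann-Whitney tests.

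The source is set out under Examinations and measurements 2 and 4 years after operation. Item 3 is "Journal examination in regards to complications and new drain operations". Item 4 is "If required the GPs journal may be requested". Item 3 does not say whose journal is examined. Because the GP's journal is a separate item, the hospital's is the natural reading.

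Contact differs by arm (Design and procedure). For the hospital arm, "Follow-up through the hospital involves a control every 6 months as long as there is a clinical need for it". The GP arm is seen on demand only, and "GPs will receive a procedure for controls and how one should tackle the most common complications". Under Ethics, the GP is to send the child back to hospital if complications or worsening occur.

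The health-economic section plans NPR and KUHR/KPR data with diagnosis and procedure codes, including "Level of care (hospital, GP, GP acute and emergent)". Under Ethics, these data need an additional consent.

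SAP section 4.1 gives the aim as determining whether "controls performed by the GP are a safe and sufficient alternative to those controlled within the specialist health care system". SAP section 9 (Safety analyses) observes that complications often arise between standard controls and go to the GP. It defines no complication outcome, source or comparison.

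**The concern.** A between-arm comparison of event rates is fair only if an event has about the same chance of being recorded in either arm. Here the default source is fed by routine visits in one arm only. A complication noted at a six-monthly hospital control enters the journal that is examined. The same complication treated by the GP, under the procedure the GP has been given, stays in a journal that is opened only at someone's discretion.

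The expected error favours GP follow-up, which is the option under test. In its Background section the protocol faults the earlier retrospective study for not examining complications beyond re-operations. Without a firmer source rule, this trial risks repeating that weakness for complications treated in primary care.

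**Working it through.** **What the documents supply.** They give the sample size (135 per group, SAP 5.3) and the test level (two-sided 5%, SAP 6.1). They give no complication rate, margin, power or capture fraction, so there is no figure of the plan's own to reproduce for this endpoint.

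**Check of the method on the nearest stated figure.** For middle-ear fluid, 90% against 85%, the protocol (Number of participants) states 680, 920 and 1110 per group for 80%, 90% and 95% power. The two-proportion formula with pooled variance under the null and no continuity correction gives 686, 918 and 1135, all within 3%. The same normal approximation is used below.

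**Which events are exposed to the problem.**
- Re-operations, and complications referred back: these should reach the hospital journal in both arms.
- Events noted at a routine hospital control: hospital journal, hospital arm only.
- Events treated wholly by the GP: GP journal, in either arm. The GP arm has no routine hospital visit at which an interim event could later be noted.

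The gap therefore mainly concerns the third group.

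**Formulas.** Let π be the true rate (equal in both arms), c_H and c_G the shares of events captured in the hospital and GP arms, and n = 135 per arm.
- Observed rates: p_H = π·c_H and p_G = π·c_G.
- Observed risk ratio under equal true rates: c_G / c_H. Only the difference in capture matters. If c_G = c_H, the ratio is 1.00 at any level of capture.
- Chance of a significant result favouring the GP arm: Φ[(p_H − p_G − 1.96·s0) / s1], where s0 = √(2·p̄(1 − p̄)/n), p̄ is the mean of the two observed rates, and s1 = √(p_H(1 − p_H)/n + p_G(1 − p_G)/n).

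**One case in full** (π = 30%, c_H = 95%, c_G = 50%). p_H = 0.30 × 0.95 = 0.285, p_G = 0.30 × 0.50 = 0.150 and p̄ = 0.2175. Then s0 = √(2 × 0.2175 × 0.7825/135) = 0.0502 and s1 = √(0.285 × 0.715/135 + 0.150 × 0.850/135) = 0.0495. The chance is Φ[(0.135 − 1.96 × 0.0502)/0.0495] = Φ(0.74), about 77%.

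**Range.** π and both capture shares are assumptions.

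| True rate | Capture, hospital arm | Capture, GP arm | Observed, hospital vs GP | Chance of false GP advantage |
|---|---|---|---|---|
| 30% | equal | equal | equal | 2.5% |
| 30% | 75% | 70% | 22.5% vs 21.0% | 5% |
| 30% | 75% | 60% | 22.5% vs 18.0% | 15% |
| 30% | 75% | 50% | 22.5% vs 15.0% | 35% |
| 30% | 95% | 70% | 28.5% vs 21.0% | 30% |
| 30% | 95% | 50% | 28.5% vs 15.0% | 77% |
| 30% | 95% | 40% | 28.5% vs 12.0% | 93% |
| 10% | 75% | 50% | 7.5% vs 5.0% | 13% |

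The same mechanism can hide a real excess. With 90% capture in the hospital arm and a true hospital rate of 20%, the observed rate is 18%. A true GP-arm rate of 0.18/0.70 = 26% (70% capture) or 0.18/0.50 = 36% (50% capture) would look identical.

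**The case against.** A reader might infer that complications are in fact under-counted in the GP arm, and that the trial's safety conclusion is therefore biased. The documents do not support that much, for five reasons.

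- **The hospital journal is an inference.** It is a reasonable one, but nothing stops the GP journal being requested for every child.
- **A trigger could exist.** Guardians report ear complaints in both arms at 2 and 4 years. SAP 5.5 also mentions questionnaires about the controls performed by the GP or in specialist care. Either could prompt a request. What is missing is a written rule.
- **Referral protects the severe end.** Severe complications are the likeliest to be referred and so to appear in the hospital journal in both arms.
- **Hospital-arm capture is incomplete too.** SAP section 9 sends complications between controls to the GP without distinguishing arms. The protocol's Background reports that many children in the earlier study saw both levels of care and that hospitals struggle to keep to control schedules. The 95% capture rows are thus hard to defend, and at 75% the chance falls to between 5% and 35%.
- **The main claim rests elsewhere.** The SAP's hypothesis concerns PTA, measured in both arms by audiographers blinded to group. No section ties the safety conclusion to the complication count.

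All five stand, and they limit the certainty, size and severity of the point. They do not remove it. The ear questionnaire (OM 8-30) looks back only 3 months, no section makes guardian report or register data the source of the complication count, and an episode resolved by the GP need leave no hospital trace. Applied as written, the rule lets capture depend on allocation.

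**Conclusion.** The point holds as a design risk to one secondary endpoint. The journal rule allows complications treated only by the GP to be missed more often in the GP arm, and the expected direction favours GP follow-up. The size cannot be derived from the documents. Under a 30% true rate in both arms and 135 per arm, all with assumed capture, the chance of a false significant GP advantage is about 5% if capture differs by 5 points (75% against 70%), and about 77% or more if it differs by 45 points or more (95% against 50%). With equal capture it is 2.5%. The primary endpoint is unaffected, and re-operations and referred complications should be largely unaffected. This should be fixed, but it does not threaten the trial's main result. Until it is fixed, the between-arm complication test should not be offered as evidence of safety.

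**What to change.** **Protocol, Examinations and measurements 2 and 4 years after operation, item 4.** Replace the optional request with one source rule applied identically to every child in both arms. The preferred source is the NPR and KUHR/KPR contacts already planned for the health-economic analysis, which cover hospital, GP and emergency care. The alternative is the GP journal for all consenting children. Define in advance which entries or codes count as a complication, and have events classified blind to arm.

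**SAP section 9.** Make this count the complication comparison, as a between-arm difference with a 95% confidence interval. Report source coverage and consent by arm. Report complications found only in the hospital journal descriptively, without a test.

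**Remaining limitation to state.** A common source gives symmetric reading of records, not fully symmetric detection. Because GP contact is on demand, fewer minor events may be noticed in the GP arm whichever source is used.

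**Cost.** Wording in both documents and some abstraction or coding time, with no new visits or tests. Records can be read retrospectively, and the protocol's timeline runs to 2027. The main drawback is that register linkage needs the added consent, so coverage will be incomplete.
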